## Abstract

**Introduction:**

A considerable burden of the tuberculosis (TB) epidemic is found in adolescents. The reasons for increased susceptibility to TB infection and higher incidence of TB disease in adolescence, compared with the 5–10 years old age group, are incompletely understood. Despite the pressing clinical and public health need to better understand and address adolescent TB, research in this field remains limited.

**Methods and analysis:**

Teen TB is an ongoing prospective observational cohort study that aims to better understand the biology, morbidity and social context of adolescent TB. The study plans to recruit 50 adolescents (10–19 years old) with newly diagnosed microbiologically confirmed pulmonary TB disease and 50 TB-exposed controls without evidence of TB disease in Cape Town, South Africa, which is highly endemic for TB. At baseline, cases and controls will undergo a detailed clinical evaluation, chest imaging, respiratory function assessments and blood collection for viral coinfections, inflammatory cytokines and pubertal hormone testing. At 2 weeks, 2 months and 12 months, TB disease cases will undergo further chest imaging and additional lung function testing to explore the patterns of respiratory abnormalities. At week 2, cases will complete a multicomponent quantitative questionnaire about psychological and social impacts on their experiences and longitudinal, in-depth qualitative data will be collected from a nested subsample of 20 cases and their families.

**Ethics and dissemination:**

The study protocol has received ethical approval from the Stellenbosch University Health Research Ethics Committee (N19/10/148). The study findings will be disseminated through peer-reviewed publications, academic conferences and formal presentations to health professionals. Results will also be made available to participants and caregivers.

Strengths and limitations of this studyA key strength of this study is the use of multiple imaging methods and respiratory function testing modalities to delineate the patterns of structural and functional respiratory abnormalities in adolescent pulmonary tuberculosis (TB).Our longitudinal study design will permit us to characterise the sociological and psychological impact of both drug-susceptible and multidrug-resistant TB on adolescents over time.The comprehensive measurement of pubertal hormones, viral coinfections and inflammatory cytokines relevant to TB biology will contribute to identifying host factors that impact the human immune response to *Mycobacterium tuberculosis*.The small sample size and susceptibility to loss to follow-up are limitations of this study.

## Introduction

There are an estimated 1.6 billion adolescents (aged 10–19 years) living in the world today, with 90% in low/middle-income countries (LMICs).^1 2^ Modelling studies suggest that 750 000 adolescents develop tuberculosis (TB) disease each year globally,^3^ yet adolescent TB remains a neglected field of research. Adolescents have unique biological and social circumstances that differ from both younger children and adults. These include hormonal and immunological pubertal changes, increasing autonomy, extensive socialisation and risk-taking behaviour. These unique features have been poorly studied in resource-limited settings, particularly in relation to their impact on health.

For reasons incompletely understood, the risk of progression from TB infection to TB disease rises in adolescence.^4^ This may be related to the impact of puberty on the immunological response to *Mycobacterium tuberculosis (Mtb*),^4^ or due to coinfections, nutrition and substance abuse (alcohol, smoking, illicit drugs) impacting on TB pathogenesis, as well as changes in social life impacting on exposure risks. Adolescents tend to develop infectious, cavitary forms of disease,^5–9^ thus having a greater impact than younger children on TB transmission. Furthermore, there is extensive social mixing,^3 5^ late presentation of TB disease,^10^ poor adherence to treatment and follow-up and high rates of loss to follow-up.^11^ These may all have a substantial impact on TB within the adolescent population and on propagation of the epidemic.^6^ Outcomes for adolescents with TB are worse than most other population groups.^12^ Treatment challenges are more complex when multidrug-resistant TB (MDR-TB; defined as disease caused by *Mtb* resistant to at least rifampicin and isoniazid) is present or when there is HIV coinfection.^13^ Finally, the impact of TB on respiratory morbidity in adolescents is almost entirely unexplored. Emerging evidence in adults demonstrates that more than half of individuals develop clinically relevant respiratory morbidity post pulmonary TB,^14 15^ and there is evolving appreciation that respiratory insults in childhood and adolescence have lifelong consequences.^16 17^ Any functional impairment may have an impact on their quality of life, their future educational and employment potential, as well as their long-term health.^18 19^ This illustrates the importance of exploring both pulmonary function and psychosocial aspects of adolescent TB in research.

TB has been identified as a key research priority for adolescent health in LMICs,^20^ and adolescent TB is a crucial component of the revised WHO Roadmap for ending TB.^21^ We therefore set out to conduct a study to examine the biology, morbidity and psychosocial contexts of adolescent TB, named Teen TB. This study will provide a vehicle to explore how these different elements of adolescent TB interact. Teen TB will also allow an unparalleled opportunity to explore the patterns of abnormalities found on chest radiography, ultrasound imaging and ^18^F-fluorodeoxyglucose (FDG) positron emission tomography (PET) combined with chest radiography and chest CT in adolescents with TB. In addition, it will enable these findings to be correlated with the extent of respiratory deficit, social contexts and biological markers. Understanding this will inform our understanding of adolescent TB treatment, adherence and transmission and will have implications for future interventional studies.

### Study objectives

The Teen TB study has three main objectives. The first is to evaluate the relationship between baseline lung imaging (advanced and point of care) and respiratory function in adolescents with TB disease. We aim to test the hypothesis that imaging at the time of diagnosis can predict future lung function. The second objective is to explore the psychosocial experience of adolescents affected by drug-susceptible (DS) and MDR-TB and evaluate if the diagnosis of TB is associated with experiences of stigma. The third objective is to explore how pubertal hormones and viral coinfections (notably cytomegalovirus (CMV)) influence the immune response to *Mtb*. We hypothesise that as adolescents pass through puberty, they generate an increasingly pronounced myeloid inflammatory response to *Mtb*.

## Methods and analysis

### Study design and setting

Teen TB is a prospective observational cohort study which plans to recruit 50 adolescents (10–19 years) with newly diagnosed microbiologically confirmed TB disease (including both MDR-TB and DS-TB) in Cape Town, Western Cape, South Africa and follow them over a 12-month period. We will also recruit 50 TB-exposed controls (exposed to both DS-TB and MDR-TB). South Africa’s Western Cape province is highly endemic for TB and previous studies have shown a substantial burden of TB among adolescents in this setting.^12^ The overall TB incidence rate in the Western Cape was 681/100 000 in 2015 and, in a study from the same province, the incidence of TB in adolescents was found to be 450/100 000.^22 23^ In 2020–2021, the estimated HIV incidence rates for adults aged 15–49 years in the Western Cape was 0.51%.^24^ This high burden setting is an ideal place to carry out adolescent TB studies to meet research gaps.

### Study participants

Any adolescent with newly diagnosed pulmonary TB bacteriologically confirmed on sputum (Xpert-positive or culture-positive), with or without HIV coinfection and who are within the first 14 days of treatment, are eligible to participate in this study. Any adolescent exposed in their household to a case of infectious pulmonary TB and who has no symptoms of TB will be considered for the TB-exposed control group. Those with TB disease will be excluded from the study if they have extrapulmonary TB without evidence of pulmonary TB. TB-exposed controls will be excluded if they have previously recovered from TB disease or if asymptomatic TB disease is suspected and/or diagnosed by baseline study investigations. Those suspected of having asymptomatic TB disease will be considered for the TB disease group if they meet the inclusion criteria. Both participants with TB disease and TB exposure will be excluded if they have a severe illness or any condition causing the adolescent to be clinically unstable or requiring intensive care treatment, if pregnant or breast feeding, if known to have diabetes mellitus and if HIV testing is declined with no recent (<12 months) HIV test result available (table 1).

**Table 1 T1:** Inclusion and exclusion criteria for Teen TB

	Inclusion	Exclusion
**Tuberculosis disease**	Any adolescent (10–19 years) who: Has a primary diagnosis of newly diagnosed pulmonary TB bacteriologically confirmed on sputum (Xpert-positive or culture-positive), with or without HIV coinfection Is within the first 14 days since diagnosis and thus 14 days of TB treatment	Extrapulmonary TB without evidence of pulmonary TB Severe illness or any condition causing the adolescent to be clinically unstable or require intensive care treatment Pregnancy or breast feeding (due to exposure to ionising radiation) Diabetes mellitus (due to the potential confounding effects of hyperglycaemia and insulin levels on ^18^F-FDG uptake on PET/CT) Participants declining HIV testing for whom a recent (<12 months) HIV test result is not available
**Tuberculosis exposure**	Any adolescent (10–19 years) who: Has been exposed in their household in the last 6 months to a case of infectious pulmonary TB Has no symptoms of TB disease	Previous TB disease Asymptomatic TB disease Severe illness or any condition causing the adolescent to be clinically unstable or require intensive care treatment Pregnancy or breast feeding (to avoid any confounding in comparison with cases) Diabetes mellitus (to avoid any confounding in comparison with cases) Participants declining HIV testing for whom a recent (<12 months) HIV test result is not available

^18^F-FDG, 18F-fluorodeoxyglucose; PET, positron emission tomography; TB, tuberculosis.

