### Blood sample collection

At baseline, all adolescents will be offered an HIV test. If they have not had a test in the last 12 months, blood will be drawn to perform an HIV ELISA. If their HIV status is available from a recent result (from the past 12 months), then this result will be used. Any participant with a new HIV infection diagnosed during this study will be counselled appropriately by a trained member of the research team and referred to routine services for evaluation and initiation of antiretroviral treatment. Participants with TB disease and TB-exposed participants will also have blood collected at baseline for CMV quantitative IgG, RNA sequencing, hormone profiling (including dehydroepiandrosterone sulfate, leptin, testosterone, oestradiol and progesterone levels) and for a panel of inflammatory cytokines relevant to TB biology, selected from previous work by the study team and from the literature. In TB-exposed individuals, blood will be taken for an interferon-gamma release assay. Participants with TB disease will undergo an additional blood draw at 2 months and samples will be stored for later analysis.

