#### Assessment of study endpoints/primary objectives

Descriptive analysis will be used to characterise the study populations, to compare the TB case and TB-exposed groups and aid in identifying differences between groups with respect to potential confounders. Categorical variables will be expressed as percentages and continuous variables will be expressed as mean±one SD or median with IQR, depending on the distribution of the data.

In those with TB disease, we will categorise disease on CXR as severe and non-severe, using established criteria^29^ and will compare mean z-score of FVC, FEV1 and FEV1/FVC ratio at 2 months and 12 months in those with severe and non-severe disease using a paired sample t-test. We will also evaluate the relationship between severe and non-severe disease on CXR with other measures of functional tests (oscillometry, diffusion capacity, plethysmography, 6MWT and SGRQ). We will perform similar analyses evaluating the ability of ultrasound, CT and ^18^F-FDG PET-CT to predict different measures of lung function at 2 months and 12 months. We will compare the lung function of adolescents with TB disease and those with TB exposure using multivariable logistic regression to adjust for potential confounders and to determine the impact of TB on lung health. From a radiology perspective, we will evaluate the ability of CXR and lung ultrasound to identify findings as seen on CT chest (considered as the imaging ‘gold standard’ for this analysis) using either contingency tests or receiver operating characteristic (ROC) analysis, where appropriate.

Further multivariable analyses will be performed to explore the impact of pubertal hormones on inflammatory cytokines and how the inflammatory cytokines of adolescents with TB disease and TB exposure differ. Immune responses to viral coinfections in participants with TB disease and those with TB exposure will also be compared using regression analysis. Analyses will be performed using STATA (V.17 STATA Corp.).

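### The imaging-severity contrast in cases is fixed as a t-test without covariates, which can address prediction but not a relationship beyond HIV status and previous TB

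*Protocol article*

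**What the plan says.** **Who is a case.** Study participants and Table 1 (Protocol article) admit adolescents whose pulmonary TB is "bacteriologically confirmed on sputum (Xpert-positive or culture-positive), with or without HIV coinfection". Previous TB disease appears among the exclusions for TB-exposed controls, but not among those for cases.

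**What is known about each case.** Table 1 excludes "Participants declining HIV testing for whom a recent (<12 months) HIV test result is not available", and Blood sample collection adds that "At baseline, all adolescents will be offered an HIV test". HIV status is therefore complete by design. Clinical data collection provides for a TB history at each visit.

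**What is tested.** The first aim under Study objectives is worded in two ways: to evaluate how baseline imaging relates to respiratory function, and to test whether imaging at diagnosis predicts later function. Assessment of study endpoints/primary objectives then names the analysis. After classing chest X-rays as severe or non-severe, the investigators will "compare mean z-score of FVC, FEV1 and FEV1/FVC ratio at 2 months and 12 months in those with severe and non-severe disease", by a paired-sample t-test. It continues: "We will perform similar analyses evaluating the ability of ultrasound, CT and" PET-CT.

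**Where adjustment is planned.** For lung function, the same section states adjustment only when comparing "adolescents with TB disease and those with TB exposure using multivariable logistic regression to adjust for potential confounders". The other multivariable or regression analyses concern hormones, cytokines and immune responses to viral coinfection. HIV is not named as a covariate, stratum or subgroup in any analysis.

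**The concern.** If HIV or an earlier TB episode affects both how the chest looks on imaging and how well the lungs work, the severe minus non-severe difference mixes that influence with the disease now seen on imaging. The Introduction makes the point plausible for earlier TB, reporting that in adults "more than half of individuals develop clinically relevant respiratory morbidity post pulmonary TB". Z-scores do not remove it: the sample-size section describes the reference standards in terms of age and height, not HIV or TB history.

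A t-test has no place for covariates. This is therefore a method the article has chosen, not a detail left open for an analysis plan, and an adjusted model is named for a different comparison in the same paragraph. At stake is the half of the first objective that asks about a relationship. As planned, the result could not show whether imaging tells a clinician anything beyond HIV status and TB history, which are already known.

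**Working it through.** **1. The plan's own figure.** Power and sample size assumes means of 100% and 90%, SD 15%, power 90% and alpha 0.05. Two-sided, n per group = 2 × (1.960 + 1.282)² × 15² / 10² = 2 × 10.51 × 2.25 = 47.3, against 47 stated. The figure reproduces apart from rounding. It concerns 50 cases against 50 controls, however, and not this contrast. Only the standardised difference 10/15 = 0.667 is carried forward, as a benchmark.

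**2. Precision of the contrast within cases.** With 50 cases split 25/25 and residual SD 1 (both assumed), the standard error is √(1/25 + 1/25) = 0.283 SD. Power for 0.667 SD is about 64%, and about 46% at a 40/10 split.

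**3. Bias of the unadjusted difference.** For a binary factor,

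bias = [P(factor | severe) − P(factor | non-severe)] × effect on z.

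The documents give no prevalence among adolescent TB cases (Study design and setting has only an adult HIV incidence of 0.51%), no effect, and no severity split by factor. Assumed:

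- HIV in 5–20% of cases, classed severe in 30% of HIV-positive and 60% of HIV-negative cases.
- Previous TB in 10–20% of cases, classed severe in 80% with and 50% without it.
- Effect of either factor: −0.5 to −1.0 z.

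Example, HIV at 10%: P(HIV | severe) = 0.03/(0.03 + 0.54) = 0.053; P(HIV | non-severe) = 0.07/(0.07 + 0.36) = 0.163; gap −0.110; bias +0.055 to +0.110.

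| Factor and prevalence | In severe | In non-severe | Bias, effect −0.5 | Bias, effect −1.0 |
|---|---|---|---|---|
| HIV 5% | 0.026 | 0.084 | +0.029 | +0.059 |
| HIV 10% | 0.053 | 0.163 | +0.055 | +0.110 |
| HIV 20% | 0.111 | 0.304 | +0.097 | +0.193 |
| Previous TB 10% | 0.151 | 0.043 | −0.054 | −0.108 |
| Previous TB 20% | 0.286 | 0.091 | −0.097 | −0.195 |

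A positive bias shrinks a deficit in the severe group and a negative one enlarges it. The largest entry is 0.195/0.283 = 0.69 of a standard error.

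**4. Both factors together.** Adding the biases, which is approximate, 10% of each gives 0.055 − 0.054 = +0.001 at an effect of −0.5, and 0.110 − 0.108 = +0.002 at −1.0. The extreme combinations are 0.193 − 0.054 = +0.139 and 0.029 − 0.195 = −0.166. The cancelling depends on the assumed directions: if HIV-positive cases were more often classed severe, the two biases would add.

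**5. Effect on the test (HIV only).** Simulation used 20,000 runs per scenario, 25 versus 25 cases, an HIV effect of −0.5 to −1.0 z, and HIV prevalence of 10% in one severity group. It compared an independent-samples t-test with a linear model that includes HIV. The gaps in step 3 are 6 to 19 points.

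| Gap in HIV prevalence | False positives, unadjusted | Power for 0.667 SD, unadjusted, HIV commoner in non-severe | Power, adjusted |
|---|---|---|---|
| 0 points | about 5% | 60–63% | 63% |
| 10 points | 5–6% | 46–56% | 62–63% |
| 20 points | 6–10% | 32–49% | 60% |

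With HIV in the model, false positives stay at about 5%. A 30-point gap gives 0.15–0.30 z and 8–16% false positives, but 10% against 40% means 25% HIV overall, outside the range in step 3. Previous TB was not simulated.

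**The case against.** The strongest reply is that the stated hypothesis is predictive. If old scarring makes a film look severe and lung function is later low, imaging has predicted correctly, and adjusting for previous TB would remove part of what it is meant to predict. This stands. A reader might infer that such damage creates a false imaging effect, or that the planned test is invalid. The documents do not support either reading, because nothing limits the objective to damage from the current episode. What the reply leaves unanswered is the other wording of the objective, the relationship between imaging and function.

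Second, no section links HIV to imaging appearance or to spirometry, the morbidity statement concerns adults, and the criteria for a severe film are only cited. This also stands: the mechanism is plausible, not documented. A case described as newly diagnosed might also be read as a first episode, in which event the previous-TB part would be empty. The article does not say so, and it excludes previous TB for controls only.

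Third, every prevalence and effect above is assumed, the biases can offset each other, and each is smaller than the standard error. That limits the weight of the point.

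Fourth, covariate lists are commonly left to an analysis plan. That would answer a missing list, but the article names a test that cannot take covariates.

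**Conclusion.** The point holds in a limited form. The unadjusted difference is a legitimate answer to whether imaging predicts later lung function. It does not answer whether imaging is related to lung function beyond HIV status and previous TB, and the plan contains no analysis that would.

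The size and direction of any confounding cannot be learned from the documents. They are probably modest: at most about 0.2 z for either factor alone under the assumed ranges, with partial cancelling in the assumed directions. With 5–20% HIV, about 3 to 10 of 50 cases would carry the whole HIV effect. It would go beyond the documents to say that the planned contrast is materially biased, or biased in a known direction. This is a low-cost improvement to the analysis, not a defect that undermines the study.

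**What to change.** In Assessment of study endpoints/primary objectives, replace the t-test with a linear model of each z-score (FVC, FEV1, FEV1/FVC) at 2 months and at 12 months on imaging severity. Use the same form for chest X-ray, ultrasound, CT and PET-CT. Report two results side by side:

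- the unadjusted between-group difference, as the answer on prediction;
- the difference adjusted for HIV status (yes/no) and previous TB (yes/no), as the answer on relationship.

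This also removes the paired test, which does not suit severe and non-severe cases because they are different participants. A sensitivity analysis in HIV-negative cases is optional; with very few HIV-positive cases it would nearly repeat the main analysis.

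The cost is wording only, since both variables come from data already collected. The adjusted model uses two further degrees of freedom: 50 − 2 = 48 becomes 46. If few cases are HIV-positive, the HIV coefficient will be imprecise and should not be interpreted in its own right. With at most 50 cases, the covariate list should stay this short.

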### Recruitment process

DS-TB recruitment will be carried out in collaboration with clinical staff in health facilities in the Tygerberg, Mitchell’s Plain and Khayelitsha subdistricts of the City of Cape Town Metropole. As adolescents present to health facilities in these subdistricts with TB symptoms, we will approach them and sensitise them to the study. If they are diagnosed with DS-TB and meet the eligibility criteria, we will approach them prior to starting TB treatment to see if they would be willing to participate. If willing to participate, informed written consent will be obtained from parents/legal guardians for those under 18 years with additional assent from the adolescent, whereas 18-year and 19-year olds can provide consent for themselves. Initial consultations will take place at their homes, local clinics or at Desmond Tutu TB Centre (DTTC) field sites, as determined to be most convenient to the participant and their family. Given the necessity for all participants to undertake lung function testing at Tygerberg Hospital and to undergo ^18^F-FDG PET-CT imaging for those with TB disease, the follow-up visit will be at the iKamva Unit on the Tygerberg Campus of Stellenbosch University (SU).

MDR-TB recruitment will be carried out using the established tuberculosis child multidrug-resistant preventive therapy (TB-CHAMP) trial platform to identify adolescents aged 10–19 years in the Metropolitan area who are newly diagnosed with MDR-TB disease. TB-CHAMP is an ongoing MDR-TB prevention trial that randomises children who have been exposed to MDR-TB in their household to levofloxacin or placebo, with three South African sites, and in collaboration with the MRC Clinical Trials Unit at University College London. The TB-CHAMP trial team identifies every MDR-TB patient in the Cape Town Metropolitan area through laboratory and clinical sources. This is an established platform by which adolescent MDR-TB cases can be identified. We will then, using our established links with routine services, and in collaboration with their healthcare providers, contact these adolescents, following sensitisation to the study by local clinics, ideally prior to starting MDR-TB treatment, and invite them to join the study.

TB-exposed controls are recruited from the same clinics where individuals with TB disease are recruited, and the contacts of the enrolled cases will also be eligible for inclusion. TB-exposed controls must have been exposed to an infectious DS-TB case within the last 6 months. We will again use the TB-CHAMP platform to aid in identifying adolescents who have been exposed to an infectious pulmonary MDR-TB case in the household within the last 6 months.

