### Statistical analysis

#### Power and sample size

While multiple different analyses are planned for the different components of the study (clinical, immunology, radiology, social science, virology), we calculated the sample size based on ability to detect differences in lung function. Even within this discipline, several lung function parameters will be measured during this study, but sample size calculations were performed based on assumptions related to spirometry. A reduced FVC, compared with age and height reference standards, indicates restrictive lung disease, whereas a reduced FEV1 and FEV1/FVC ratio, compared with reference standards, indicate obstructive lung disease. Both patterns of lung disease have been seen in adults following pulmonary TB. To demonstrate a difference between healthy individuals in our context (assumed to have a FEV1/FVC ratio of 100%; SD: 15%), and adolescents with pulmonary TB disease (assumed to have a ratio of 90%), with 90% power and an alpha of 0.05, we would need 47 adolescents with pulmonary TB and 47 healthy controls. Therefore, we plan to recruit 50 cases and 50 controls given the uncertainty in these estimates and to allow for any lost data or incomplete evaluations.

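### Household contacts of enrolled cases may serve as controls, but neither the sample size nor the named case-control regressions allow for household correlation, so standard errors may be biased in either direction

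*Protocol article*

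**What the plan says.** Under Recruitment process, the protocol article gives two overlapping sources of controls. The first is clinic-based: "TB-exposed controls are recruited from the same clinics where individuals with TB disease are recruited". The second is the circle around the study's own cases, because "the contacts of the enrolled cases will also be eligible for inclusion". It also uses the TB-CHAMP platform to find adolescents exposed to MDR-TB at home. Table 1 requires of each control that he or she "Has been exposed in their household in the last 6 months to a case of infectious pulmonary TB". A contact of an enrolled case who qualifies through that exposure therefore normally lives with the case. No section caps the number of controls per household, and none says that several will be taken from one.

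Under Power and sample size, the calculation compares healthy individuals, "assumed to have a FEV1/FVC ratio of 100%; SD: 15"%, with cases at 90%, and arrives at 47 per group, raised to 50.

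Under Assessment of study endpoints/primary objectives, lung function is compared between cases and "those with TB exposure using multivariable logistic regression to adjust for potential confounders and to determine the impact of TB on lung health". Further multivariable analyses address "how the inflammatory cytokines of adolescents with TB disease and TB exposure differ", and immune responses to viral coinfections are compared by regression. No household term, matching or robust variance is mentioned. Independence of participants is not asserted either.

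**The concern.** People in one household share home environment and socioeconomic conditions, and often genes. Lung function, cytokine levels and CMV serology can therefore be correlated within a household. An ordinary regression assumes independent observations, and the recruitment rule allows that assumption to fail in two ways that act in opposite directions.

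- **A case and a control from one household.** Their shared component cancels in the case-control difference. The usual standard error is then too large, the interval too wide, and information is lost.
- **Several controls from one household.** They carry less information than the same number of unrelated controls. The usual standard error is then too small.

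At stake are the intervals and p-values of the TB versus TB-exposed comparisons (lung function, cytokines, viral coinfection), whichever regression is fitted. With 50 per group, in a study that lists small sample size among its own limitations, avoidable loss of information matters.

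**Working it through.** **1. The plan's own figure.** Inputs from Power and sample size: difference 100 − 90 = 10 points, SD 15, power 90%, alpha 0.05 (taken as two-sided).

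n per group = 2 × (1.960 + 1.282)² × 15² / 10² = 47.28.

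This agrees with the stated 47 when rounded to nearest (48 when rounded up). The stated figure is thus an independent-groups calculation with no term for household correlation. At 50 per group the standard error of the difference is 15 × √(2/50) = 3.0 and the power is 91.5%.

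**2. Formula with shared households.** Take n per group, a common SD s, and a correlation ρ between any two members of one household. Let f be the share of controls who each live with one enrolled case, and c the average number of other enrolled controls in a control's household.

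- Variance of the control mean: (s²/n)(1 + cρ)
- Variance of the case mean: s²/n
- Covariance of the two means: fρs²/n

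Divide the variance of the difference by its independent value 2s²/n:

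variance ratio = 1 + cρ/2 − fρ; true/naive SE ratio = its square root.

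**3. Illustration.** The values of f, c and ρ are assumptions; the document gives none of them. Half the controls are affected, and ρ is 0.2 or 0.4.

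| Situation | ρ | Variance ratio | SE ratio | True size of nominal 5% test | Power with correct SE, 50 + 50 |
|---|---|---|---|---|---|
| Half the controls live with a case (f = 0.5, c = 0) | 0.2 | 1 − 0.10 = 0.90 | 0.95 | 3.9% | 94.0% |
| Same | 0.4 | 1 − 0.20 = 0.80 | 0.89 | 2.8% | 96.1% |
| Half the controls come in pairs (f = 0, c = 0.5) | 0.2 | 1 + 0.05 = 1.05 | 1.02 | 5.6% | 90.2% |
| Same | 0.4 | 1 + 0.10 = 1.10 | 1.05 | 6.2% | 88.8% |

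In the first situation, ignoring the link is like discarding 10% to 20% of the sample, since the true variance is 0.90 to 0.80 of the one used.

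**4. Offsetting.** The ratio is exactly 1 whenever c/2 = f. Examples are two controls in every control household with half of those households holding a case (c = 1, f = 0.5), or three controls in each with every household holding a case (c = 2, f = 1).

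**5. Wider range.** With ρ from 0.05 to 0.5, one to three controls per household and f from 0 to 1, the SE ratio runs from 0.71 (ρ = 0.5, one control in each case's household) to 1.22 (ρ = 0.5, three controls per household, none with an enrolled case). For ρ up to 0.3 it runs from 0.84 to 1.14.

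**6. Limit of the calculation.** It describes an unadjusted difference in means. The plan names adjusted regressions, logistic for lung function, so the figures show order of size and direction only.

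**The case against.** The strongest case against is that the point rests largely on silence. The statistical section is a short summary in a journal article, and a variance option or a linking field is the kind of detail left to a full protocol, case report form or analysis plan, none of which is shown. Controls also come from clinics and TB-CHAMP without any link to an enrolled case. The eligibility rules (age 10 to 19, no symptoms, no previous TB, not pregnant, no diabetes) restrict how many contacts per household can qualify. Socioeconomic data are collected, and adjusting for them should lower the residual household correlation. On the illustrative figures the effect is modest, and the case-control link makes the usual analysis conservative, not invalid.

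Much of this stands, and it rules out three stronger readings that a reader might infer:

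- **That several controls will come from one household.** The document only fails to exclude it.
- **That the analysis treats everyone as independent.** Only the sample-size formula shows this; the analysis section names no allowance but does not rule one out.
- **That the standard errors are wrong.** They may be too large, too small or about right, depending on quantities that are not given.

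What does not stand is that nothing is left. The document itself states the recruitment rule that creates household links, the independent-groups sizing and the regressions. Followed as written, those regressions do not reflect the recruitment rule. Data management and confidentiality also says that addresses are kept apart from research data, which are linked only to the study number. Unless a household code is made on purpose, an analyst may be unable to see who shares a home.

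**Conclusion.** The point holds as a possible bias of unknown sign and probably modest size. The design allows household-linked participants, the sizing assumes independent groups, and "using multivariable logistic regression to adjust for potential confounders" is stated without any allowance for household. With half the controls affected and a correlation of 0.2 to 0.4, the true standard error of an unadjusted mean difference is about 0.95 to 0.89 of the naive one when controls live with cases, and about 1.02 to 1.05 of it when controls come in pairs. If both occur, the effects partly or wholly cancel; if no households are shared, there is no effect. The share and the correlation are assumptions. This does not undermine the study; it is a worthwhile and inexpensive improvement to the case-control analyses.

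**What to change.** 1. Derive a household identifier that links each control to an enrolled case and to other enrolled controls at the same home, using recruitment records and the addresses already held. Someone with access to the identifiers should make the link and pass only a coded household number to the analyst, so that the separation of identifiers from research data is kept.
2. Report how many cases and controls share a household, and in what combinations.
3. Fit the TB versus TB-exposed regressions (lung function, cytokines, viral coinfection) with standard errors clustered on household. A household random intercept is an alternative. If controls turn out to have been deliberately matched to cases, use a conditional analysis.

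The cost is a small amount of data linkage and one model option, with no new visits or measurements. It remains feasible although recruitment began in November 2020, provided the records allow the link. The statistical downside is slightly less stable standard errors in a small sample. In the illustration where 25 of 50 controls each live with one case, 100 − 25 = 75 households would remain as clusters.
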